## Abstract

**Background:**

Localised renal cell carcinoma (RCC) is usually treated surgically, with post‐operative imaging‐based surveillance to monitor for recurrence. However, surveillance practices vary widely, and patients often lack a clear understanding of their risk of recurrence and follow‐up care. The PREDICT Kidney tool has been developed to enhance risk communication by providing individualised recurrence and mortality risk estimates. The tool uses the Leibovich score augmented with English national data to provide a personalised risk assessment of cancer recurrence and death from other causes, presented in both numerical and visual formats.

**Study Design:**

A multicentre, prospective feasibility study of incorporating the PREDICT Kidney risk communication tool into the first follow‐up consultation for localised RCC patients post‐surgery.

**Endpoints:**

Patient uptake into the study, completeness of data collection, consultation duration, the acceptability of the tool to both patients and clinicians, clinician adherence to the study “best‐practice” guide, variability in tool usage across clinicians and sites and patient‐level clinical outcomes including subjective and objective comprehension of risk of recurrence and follow‐up, perceived risk of cancer recurrence, risk conviction, satisfaction with the information provided on risk of recurrence and follow‐up, and fear of cancer recurrence.

**Patients and Methods:**

We aim to recruit 60 patients from three hospitals in England and Scotland. Patients treated with surgery for primary localised clear‐cell RCC awaiting their first follow‐up appointment will be invited to take part. Participants will be allocated into two groups: standard care and standard care supplemented with the use of the PREDICT Kidney tool. Data will be collected through questionnaires, audio/video recordings of consultations and interviews with a subset of patients and clinicians. The study period is planned from September 2024 to July 2025. The findings will guide the design of a future randomised controlled trial to evaluate the tool's efficacy in clinical settings.

## BACKGROUND

1

Renal cell cancer (RCC) is the 7th most common cancer in the UK^1^ and its management increasingly requires a multi‐specialist approach.^2^ Between 70% and 75% of patients diagnosed with RCC have localised disease at diagnosis and are most commonly treated surgically^3^; however, approximately 20% subsequently develop cancer recurrence.^4^ Surveillance, including interval imaging with computerised tomography (CT) scans, is an important component of post‐operative care for these patients. However, surveillance is associated with potential harm for patients, including anxiety and radiation exposure, as well as being resource intensive for the healthcare service.

Tailoring surveillance based on individual risk of recurrence is recommended by many current guidelines,^5^, ^6^, ^7^, ^8^, ^9^ with the recommended follow‐up schedules for patients differing with respect to modality, frequency and duration depending on risk classification. No guideline recommends one specific risk model or risk threshold, leaving the choice to clinicians.^10^ In the UK, one of the most widely used risk models, which is also recommended in the recently published Getting It Right First Time (GIRFT) guidelines,^11^ is the Leibovich score.^12^ This score estimates the risk of recurrence based on tumour characteristics (size, stage, nuclear grade, presence of necrosis and regional lymph node status). Based on their score, patients are stratified into low (score 0–2), intermediate (score 3–5) and high (score above 6) risk groups for cancer recurrence, which subsequently guides their surveillance. Although the estimated metastasis‐free survival rate for the three risk categories has been published, and the score has been validated in studies for recurrence‐free survival, cancer‐specific survival and overall survival,^13^ it does not give an absolute risk of recurrence or take into consideration other competing health risks. Surveillance is also a source of anxiety for many patients^14^ and understanding of decision‐making about follow‐up is poor. In a recent study, in which we held focus groups with patients with kidney cancer to understand their experience of follow‐up care,^15^ participants described marked variation in how the risk of recurrence was communicated and a lack of transparency around decision‐making for risk‐stratified follow‐up. Some were able to recall being given their Leibovich score, whilst others reported no conversations with their clinical team about their risk of recurrence. Fear of recurrence is common in patients with localised RCC, with this affecting quality of life and health outcomes.^16^ It is also known from studies in other cancer types that patient recall of risk is often poor, with many perceiving their risk to be higher than the actual estimate.^17^

To address these issues, our team has developed PREDICT Kidney, a new online tool that presents the absolute risk of recurrence based on the Leibovich score alongside the competing age‐ and sex‐matched absolute risk of death from other causes. The tool has been co‐designed by patients, clinicians and members of the public to be used in consultations to support clinicians when communicating the risk of recurrence, with the aim that patients feel more informed about their risk of recurrence and have a better understanding of the rationale behind their planned follow‐up.

## STUDY DESIGN

2

This study is a multicentre feasibility study of incorporating the PREDICT Kidney tool into the first follow‐up consultation post‐surgery in patients with newly diagnosed localised renal cell carcinoma.

## ENDPOINTS

3

The overall aims of this study are to (a) assess the feasibility and acceptability of incorporating the PREDICT Kidney online tool into the first post‐surgery follow‐up appointments for patients with localised renal cell carcinoma and (b) to evaluate participant recruitment, completeness of data collection and estimates of patient‐level outcomes to inform the design of a future trial. The study objectives and outcome measures are described in Table 1.

**TABLE 1 bco270014-tbl-0001:** Overview of feasibility and patient‐level objectives, and their corresponding outcomes and time‐points.

Objective	Outcome	Time point
To quantify uptake into the study	The proportion of eligible patients invited to participate who consent to take part	At completion of recruitment
To assess the completeness of data collection	The proportion of patients who consent to participate in trial who go on to complete the questionnaires	At the completion of recruitment
To measure the time needed to use the tool and any change in overall length of consultation	The delivery time of the PREDICT Kidney tool during consultation appointments (intervention group only) The length of consultation appointments	Within first follow‐up consultation
To assess the acceptability of integrating the tool into clinical care to patients and clinicians	Acceptability to patients and clinicians	At interview (2–6 weeks after first follow‐up consultation)
To assess adherence to the study “best‐practice” guide by clinicians and variability between clinicians and sites in use of the tool	Clinician adherence to “best‐practice” checklist	Within first follow‐up consultation
To evaluate patient‐level clinical outcomes	Satisfaction with the information provided on risk of recurrence and follow‐up	Immediately after first follow‐up consultation
	Subjective comprehension of risk of recurrence and follow‐up	Immediately after first follow‐up consultation
	Objective comprehension of risk of recurrence	Immediately after first follow‐up consultation and at 3‐months post consultation
	Perceived risk of cancer recurrence	3‐months post consultation
	Risk conviction	Immediately after first follow‐up consultation and at 3 months post consultation
	Fear of cancer recurrence	Immediately after first follow‐up consultation and at 3 months post consultation

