### Participants and recruitment

5.1

We aim to recruit 60 participants from three centres across England and Scotland. Potentially eligible patients will be identified by members of the clinical team at each centre on a weekly basis by reviewing the appointment list for the clinic two to three weeks ahead or through the weekly multidisciplinary team meeting (MDT).

Potentially eligible patients will be sent a study pack including a cover letter on hospital‐headed paper, a participant information leaflet and a copy of the consent form. Contact details for the research team will be included in the participant information sheet and potential participants will be encouraged to contact the research team if they have any questions about the study. As participants may not know whether the excised renal mass is RCC in advance of the follow‐up consultation, the cover letter and participant information sheet will make clear that all those who have had surgery for a kidney mass are being invited and in the event that they do not in fact have cancer, they will be unable to participate in the study.

Patients potentially interested in taking part will be invited to arrive 20 minutes in advance of their follow‐up clinic appointment. Upon arrival and prior to their consultation, they will be met by a member of the clinical team who has been appropriately trained in obtaining consent for research studies. It will be explained to the patients that they can decide either to (i) participate in the study with their consultation being video and audio recorded; (ii) participate in the study with their consultation being just audio recorded; (iii) participate in the study without their consultation being video or audio recorded; or (iv) not participate in the study. For those agreeing to take part, written consent will be taken. The patients will then be given a corresponding card (green for (i), yellow for (ii), red for (iii) or no card at all for option (iv)) which they will present to their clinician upon walking into the consultation room.

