Participants will be then allocated to the ‘standard of care’ (SOC) arm or the ‘SOC and PREDICT Kidney’ (intervention) arm of the study (Figure 1). Allocation will be done such that patients at each site will be allocated to the SOC arm until a minimum of eight patients have been recruited. Subsequently, patients at each site will be allocated to the intervention arm. This approach has been chosen to reduce contamination between the arms by clinicians changing their SOC following participation in the intervention arm of the study.

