### Sample size

5.3

We aim to recruit 30 patients to each arm (a total of 60). This will enable us to assess the recruitment rate to within +/− 10% with 95% confidence intervals (point estimate 50%). This number of participants is also sufficient to enable data collection for the qualitative components of the analysis.

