**Moderators**				
Subjective numeracy	Eight questions on 6‐point scale, taken from the cognitive ability domain of the Subjective Numeracy Scale^22^	•		
Objective numeracy	Three questions with numeric answers^23^	•		
Health Literacy	Single Item Literacy Screener (SILS)^21^	•		
General Health	EQ‐5D‐5L^24^	•		

*
Intervention group only.

Three months after their consultation, study participants in both arms will be sent a final short questionnaire including measures of perceived risk of cancer recurrence and the complete Fear of Cancer Recurrence Inventory short form (FCRI‐SF) (Table 2, File S3).

To assess the fidelity of the use of the tool by clinicians and to monitor the additional time taken to deliver the intervention, a subset of both control and intervention consultations will be video recorded. A subset of study participants from the intervention arm will additionally be purposively sampled based on risk profile to take part in a telephone or online interview with a member of the research team within 2–6 weeks of their consultation. The interviews will be semi‐structured based on an interview schedule informed by the Theoretical Framework of Acceptability (TFA)^27^ and will include a discussion of the participants' experience of being told their risk of recurrence and competing risk of death from other causes using the PREDICT Kidney tool and how this has affected their understanding of their risk of recurrent disease.

All healthcare professionals participating in this study will also be invited to participate in an interview with a member of the research team. The interviews will be based on a schedule informed by the TFA,^27^ normalisation process theory^28^ and the system usability scale.^29^ They will focus on tool acceptability, perceived usability and perceived limitations and barriers to uptake.

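### Table 1 measures questionnaire completeness when recruitment ends, before the three-month questionnaire is due for the last-recruited patients

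*Protocol article*

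**What the plan says.** Section 3, Table 1 gives the completeness outcome as "The proportion of patients who consent to participate in trial who go on to complete the questionnaires", with time point "At the completion of recruitment". No questionnaire is excluded.

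Section 5.4 and Table 2 describe three questionnaires: one before the consultation, one immediately after it, and a last one: "Three months after their consultation, study participants in both arms will be sent a final short questionnaire".

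Section 5.1 places consent on the day of the consultation: "Upon arrival and prior to their consultation, they will be met by a member of the clinical team", and written consent is taken then. The same section makes allocation sequential within each site: "patients at each site will be allocated to the SOC arm until a minimum of eight patients have been recruited", and then "Subsequently, patients at each site will be allocated to the intervention arm".

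Section 5.3 plans 30 patients per arm, 60 in total. The Abstract gives a study period from September 2024 to July 2025. The length of the recruitment window is not stated.

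**The concern.** A patient's three-month clock starts on the day of consent. When the last patient is recruited, that patient's final questionnaire is still three months from being sent, and the same holds in part for everyone recruited in the preceding three months. A count taken at the stated time, with all consenting patients as the denominator, treats these patients as if they had failed to complete.

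Completeness is named in overall aim (b) of section 3 as information for designing a future trial. The third questionnaire is the one completed away from the clinic. It carries the three-month measurements that Table 1 lists for objective comprehension, perceived risk, risk conviction and fear of recurrence. An understated return rate would give the future trial too pessimistic an allowance for attrition.

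The sequential allocation adds a second effect. The last patients recruited at each site are intervention patients, so the shortfall would fall mainly on that arm.

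**Working it through.** **The plan's own figure.** The article gives no target for completeness. Its one precision statement (section 5.3, within 10 percentage points at 50% uptake) concerns the recruitment rate. Recruiting 60 patients at 50% uptake means 120 invited, and 1.96 × √(0.25/120) = 0.089, so that statement holds. This point does not affect it.

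**Inputs from the article.** 60 patients, 30 per arm; at least 8 standard-care patients at each of three sites, so at least 3 × 8 = 24; final questionnaire at 3 months; consent and consultation on the same day; study period of about 11 months.

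**Assumptions, not in the article.** Even accrual over R months, sites in step, and standard care filled before intervention. R itself is not stated. R = 8 leaves three of the 11 months for follow-up. R = 11 uses the whole study period and is an outer case, because the last questionnaires would then fall after July 2025.

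**Patients not yet due when recruitment ends** = 60 × 3/R. **Highest possible three-month completeness, overall** = (60 − not due)/60.

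- R = 6: 30 not due; ceiling 30/60 = 50%
- R = 8: 22.5 not due; ceiling 37.5/60 = 62.5%
- R = 9: 20 not due; ceiling 40/60 = 67%
- R = 10: 18 not due; ceiling 42/60 = 70%
- R = 11: 16.4 not due; ceiling 43.6/60 = 73%

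These ceilings assume that every questionnaire is returned the moment it is sent, so allowing for return time would lower them. If the assumed true return rate were 80%, the apparent overall figure would be 0.8 × 62.5% = 50% at R = 8 and 0.8 × 72.7% = 58% at R = 11.

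**Which arm the not-due patients are in.** With 30 per arm, all of them are intervention patients when 60 × 3/R ≤ 30, that is R ≥ 6. With only the minimum 24 standard-care patients and 36 intervention patients, the condition is 60 × 3/R ≤ 36, that is R ≥ 5. For shorter recruitment some standard-care patients are also not due: with 30 per arm, 6 of them at R = 5 and 15 at R = 4.

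Where all are intervention patients, the ceiling in that arm with 30 patients is (30 − 22.5)/30 = 25% at R = 8 and (30 − 16.4)/30 = 45% at R = 11. With 36 patients it is (36 − 22.5)/36 = 37.5% and (36 − 16.4)/36 = 55%. The standard-care arm is not capped.

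**What the ceilings cover.** They apply to the three-month questionnaire, and to any count that requires all three to be complete. The two clinic-day questionnaires are unaffected.

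**The case against.** The strongest reply is that no harm follows unless the team freezes the count on the last day of recruitment and scores questionnaires not yet due as missing. The article announces no interim report. Section 5.5 summarises completeness alongside the other questionnaire data and compares groups at both post-consultation time points, which requires the three-month returns. On this view the label is a loose way of saying end of study.

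That reading is possible, and the team may well intend it, but the text does not say it. Table 1 gives almost the same label to uptake, where it is meant literally, and it names the three-month point explicitly in other rows. Nor does the text limit the outcome to the clinic-day questionnaires. If it did, return of the three-month questionnaire would have no feasibility outcome in Table 1.

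Other parts of the reply stand, and they rule out stronger readings that a reader might infer:

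- *That every patient not yet due is in the intervention arm.* Allocation is sequential within each site, so a slow or late-opening site could still be recruiting standard-care patients in the final three months. The statement also needs recruitment of about six months or more.
- *That the plan will report a false difference in completeness between arms.* Table 1 defines one proportion over all consenting patients, and section 5.5 treats completeness descriptively. The arm-specific ceilings show what a split by arm would look like; the article plans no such comparison.
- *That the percentages are predictions.* They depend on even accrual and on a recruitment length that the article does not give.
- *That the study is compromised.* Sample size, allocation, data collection and the patient-level analyses are untouched. The correct proportion can be calculated later from the same records.

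Reporting completeness for each questionnaire and by arm is detail that an article may leave to the full protocol or analysis plan, so its absence is not part of this point.

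**Conclusion.** The stated time point is wrong for an outcome that includes the three-month questionnaire. This follows from Table 1, section 5.1 and section 5.4 taken together and needs no outside figure. It is a rule that conflicts with the data schedule, not an omitted detail.

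Followed literally, it leaves about 16 of 60 patients (11-month recruitment) to 22 of 60 (8-month recruitment) not yet due, and caps apparent three-month completeness at about 73% to 62.5% overall, assuming even accrual. A shorter recruitment period would lower the cap further. The patients affected would be mostly or entirely in the intervention arm, provided that recruitment lasts about six months or more and sites progress together.

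The severity is minor to moderate. The outcome is a descriptive feasibility measure, and the error can be corrected without new data, but as written it yields a misleading figure for the future trial's design.

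**What to change.** In Table 1, change the time point for completeness to after the last participant's three-month questionnaire window has closed. If completeness is reported earlier, use as the denominator only those patients whose questionnaire was due by the date of the count.

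The cost is one table cell, plus a denominator rule if there is an early report. This result is then available about three months after recruitment ends, at the same time as the three-month outcomes. No extra data collection is needed and the sample size does not change.

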## ELIGIBLITY CRITERIA

4

Participants will be eligible for inclusion in the study if they have been treated with surgery (either partial or radical nephrectomy) for primary localised clear cell RCC and are awaiting their first post‐surgery follow‐up appointment, are aged 18 years or over, are able to read and write in English and to understand and sign the written information consent form. Patients will be ineligible if they are known to have a familial syndrome predisposing them to RCC, have had surgery for a second primary kidney cancer or have any other conditions which, in the opinion of the local Principal Investigator, makes them unsuitable for study participation.

## METHODS

5

### Participants and recruitment

5.1

We aim to recruit 60 participants from three centres across England and Scotland. Potentially eligible patients will be identified by members of the clinical team at each centre on a weekly basis by reviewing the appointment list for the clinic two to three weeks ahead or through the weekly multidisciplinary team meeting (MDT).

Potentially eligible patients will be sent a study pack including a cover letter on hospital‐headed paper, a participant information leaflet and a copy of the consent form. Contact details for the research team will be included in the participant information sheet and potential participants will be encouraged to contact the research team if they have any questions about the study. As participants may not know whether the excised renal mass is RCC in advance of the follow‐up consultation, the cover letter and participant information sheet will make clear that all those who have had surgery for a kidney mass are being invited and in the event that they do not in fact have cancer, they will be unable to participate in the study.

Patients potentially interested in taking part will be invited to arrive 20 minutes in advance of their follow‐up clinic appointment. Upon arrival and prior to their consultation, they will be met by a member of the clinical team who has been appropriately trained in obtaining consent for research studies. It will be explained to the patients that they can decide either to (i) participate in the study with their consultation being video and audio recorded; (ii) participate in the study with their consultation being just audio recorded; (iii) participate in the study without their consultation being video or audio recorded; or (iv) not participate in the study. For those agreeing to take part, written consent will be taken. The patients will then be given a corresponding card (green for (i), yellow for (ii), red for (iii) or no card at all for option (iv)) which they will present to their clinician upon walking into the consultation room.

Participants will be then allocated to the ‘standard of care’ (SOC) arm or the ‘SOC and PREDICT Kidney’ (intervention) arm of the study (Figure 1). Allocation will be done such that patients at each site will be allocated to the SOC arm until a minimum of eight patients have been recruited. Subsequently, patients at each site will be allocated to the intervention arm. This approach has been chosen to reduce contamination between the arms by clinicians changing their SOC following participation in the intervention arm of the study.

